**Fig. 4 Fig4:**
[figure not shown]
ITS design with CCQ

### Participants

Three health care groups participate in this study. Therefore, COPD patients of general practices in these care groups are eligible. More specifically, patients are eligible when they are diagnosed with COPD according to GOLD criteria (post-bronchodilator FEV1/FVC < 0.7) in accordance with the Dutch general practitioners (GPs) COPD Guidelines [31] and when they are treated for COPD in primary care. The study is intended to be inclusive rather than exclusive to achieve high external validity (applicability to daily practice). Patients are excluded if they are unable to fill in questionnaires, patients that have no access to internet, patients with terminal illness, immobile patients and patients with severe substance abuse.

### Recruitment of patients and non-participation analysis

We started by recruiting primary care groups; group 1, group 2, and group 3 decided to participate in this study because they wanted to contribute to a project with a possible healthcare improvement. The general practitioners that are part of the care groups could volunteer to participate in the study; a selection of them did.

Because general practices as well as patients are free to volunteer, bias might occur in our research group. We will determine the differences in clinical status between study participants (included patients) and non-participants (eligible patients) by CCQ questionnaire, as well as gender and age differences.

### Intervention

In Fig. 5 all actions of the intervention are summarized:

**Fig. 5 Fig5:**
[figure not shown]
Interventions per group

In group 1 all caregivers (GPs as well as practice nurses) will be trained to provide COPD care according to an evidence based disease management program; subsequently they implement the COPD care program in their practices under supervision of a specialized nurse. Practice nurses will receive support by a research nurse to make sure their records of COPD patients are up-to-date and to prepare consultation with their patients according to the disease management program. In addition, all practice nurses will be trained to use the web portal and to communicate with patients according to the principles of self-management.In group 2 all caregivers (GPs as well as practice nurses) will be trained shortly to ameliorate their skills in COPD care according to an evidence based disease management program that they already use. All practice nurses will be trained to use the web portal and to communicate with patients according to the principles of self-management. The training is developed and provided for by the e-Vita study group and is based on national and international guidelines.In group 3 caregivers will not receive any training. Patients will receive a brochure how to use the web portal.

The type of intervention is adopted by the care groups after thorough consideration and discussion. The e-Vita study group determined the type of platform and the level of support.

Next, we will offer patients an online interactive care platform or web portal. The portal provides disease specific education and tips that fit their personal disease management program. In addition, the portal provides tools to report and monitor personal health goals, actions and health-related quality of life that can be shared with the patients’ own practice nurses. The portal in group 1 and 2 has better quality and more advanced possibilities for monitoring health goals with actions than the portal in group 3. The portal will be provided for a period of 15 months. Patients are informed by letter about the web portal. Patients in group 3 who agree to use the portal will receive instructions and log in information by e-mail. Patients in group 1 and 2 who agree to use the portal will be invited by their own practice nurses for intake. During intake the practice nurse defines a personal health goal together with the patient and gives instructions how and why to use the portal. Participants continue to receive regular COPD care by their GP and nurse practitioner according to the disease management program of the care group. Stable COPD patients visit their nurse practitioner yearly to check up on their disease management. The patient portal can be used by care professionals to prepare consultation or to monitor patients in-between their visits to their general practice.

Third, a subgroup of participants (1a and 2a) will receive extra support to use the portal by home visits or with instructions by telephone. During the home visit and consultation it will be checked if patients are able to log on the portal, if they understand the possibilities of the portal, and if they have started working on their personal health goal using the portal.

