Because the most powerful studies are prospective studies, we chose a prospective parallel cohort design. We asked three primary care groups to invite their COPD patients for the e-Vita study. Because there are several differences between the groups (Fig. 3), we can not compare the COPD cohorts by combining data across three different groups. We chose for an interrupted time series (ITS) design to evaluate clinical outcomes (CCQ) within each group. In ITS studies, data are collected at multiple time points before and after an intervention in order to detect whether or not the intervention has a significantly greater effect than any underlying secular trend [26]. ITS can detect changes that are delayed or intermittent. It can also determine if the change is permanent or temporary. In addition, it allows evaluation of variables which are changing before the intervention, for instance, by comparing slopes of trend lines before and after the intervention. Finally, ITS makes it easier to control for confounding variables and regression to the mean [27]. The ITS will be performed according to guidelines of the EPOC Cochrane group [25]. Although well-conducted randomised trials provide the most reliable evidence on the effectiveness of interventions, they are not feasible for our setting of an implementation design with organisational changes in a real-life health care system within three different care groups with different demands. An advantage of an ITS design is that it allows for the statistical investigation of potential biases in the estimate of the effect of the intervention.

In addition to clinical outcomes, we also want to investigate the effect of different organisational implementation methods. Therefore we will implement the platform in group 1 and 2 using different methods. Differences will be measured using a parallel cohort design. To be certain that intervention groups will be balanced in known and unknown prognostic factors in the long run we will use randomisation within group 1 and 2. To rule out human influences we will randomise online for the level of support.

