**Fig. 2 Fig2:**
[figure not shown]
Research design for the different groups and interventions of e-Vita COPD

Organisational and technical differences are depicted in Fig. 2: three different care groups and two different web portals are included. Two different methods of implementation are distinguished within group 1 and 2: one with high level of personal assistance and one with low level of personal assistance. All patients in group 1 and 2 start with a personal instruction by the primary care nurse during a regular control visit. Patients will be randomly subdivided in two groups by computer by research assistants (randomisation is computerised to prevent human influence) with high (a) and low (b) level of support. In group 1a, high level support implies home visits for patients by a research nurse who accompanies the use of the web portal. In group 2a, high level support implies telephone consultation for patients by a research nurse who accompanies use of the web portal. In group 1b and 2b low level support implies that the primary care nurse shows the patient only once how to use the web portal (the usual organisational implementation method in daily practice) without any follow-up instruction. In group 3 the web portal is offered as free use: patients will receive instructions from the web portal itself. There will be no active support from caregivers or research nurses.

The groups differ in organisation, area, use of the web portal, and integration of the portal in a COPD disease management program (Fig. 3); these characteristics are based on Dutch reports of care groups [28]:

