**Fig. 3 Fig3:**
[figure not shown]
The different characteristics of group 1, 2, and 3

Group 1 will start with COPD disease management simultaneous to implementation of the web portal. The web portal is integrated in the disease management program (integrated use).Group 2 is used to working with a COPD disease management program. They will start with the web portal, which is integrated in their own disease management program (integrated use).Group 3 is used to working with a COPD disease management program. They will start with the web portal, but the web portal is not integrated in their own disease management program (free use).

As was described above, the implementation of the portal will be studied using a prospective parallel cohort design. The clinical effects of the web portal will be investigated using an interrupted times series (ITS) study design (Fig. 4) and measured according to changes in health status with the Clinical COPD Questionnaire (CCQ, see Appendix 1). ITS design includes multiple observations over time that are ‘interrupted’ by interventions. The time intervals between the observations T1, T2, T3, and T4 are 6 months, to detect the change in CCQ in a trend and slope over the total period of time. The time intervals between the 3 measurements of each observation T1, T2, T3, and T4 is two weeks, based on the high responsiveness of CCQ [29]. The ITS will be performed according to guidelines of the EPOC Cochrane group [30]. The aim of an ITS design is to detect confounding trends by performing several measurements at specified time intervals, before and after the intervention. An advantage of an ITS design is that it allows for the statistical investigation of potential biases in the estimate of the effect of the intervention.

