### Data analysis

Along with our research design, analyses will be multilevel:To investigate the effect of the use of the web portal on the primary clinical outcomes, the ITS data will be analysed. The preferred method to analyse ITS studies is a statistical comparison of time trends before and after the intervention. Time series analysis using ARIMA models is one way of analysing the data, but there are a number of statistical techniques that can be used depending on the characteristics of the data, the number of data points available and whether autocorrelation is present. The final choice for the method to analyse the data will be made when the total set of data is available after consultation of a statistician.To investigate the effects of organisational aspects uptake of the portal will be analysed for care group 1, 2 and 3 using Chi Square tests (Fishers’ Exact Test for categorical variables and *F*-tests for continuous variables) and (repeated measures) ANOVA analyses. To analyse the effects of organizational aspects as described in the paper, the groups will be compared.To investigate the effect of integration of the web portal in daily practice, outcomes within integrated (group 1 and 2) and the free use groups (group 3) will be analysed using Chi Square tests (Fishers’ Exact Test for categorical variables and *F*-tests for continuous variables) and (repeated measures) ANOVA analyses.To investigate the effect of different organisational implementation methods, outcomes within groups with high level support (1a and 2a) and low level support (1b, 2b and 3) will be analysed using Chi Square tests (Fishers’ Exact Test for categorical variables and *F*-tests for continuous variables) and (repeated measures) ANOVA analyses.To explore correlation between self efficacy, sociodemographic characteristics on the one hand and adoption of the portal and clinical outcomes on the other hand, Pearson product-moment coefficients will be calculated across all research groups.To make a cost-effectiveness analysis, the direct costs of the different organisational implementation methods will be defined and analysed parallel to the effects of the portal in terms of Quality of Life (EQ-5D).

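### In groups 1 and 2 the interrupted time series measures the portal together with caregiver training, nurse support or a new care programme, yet the plan labels it the effect of the web portal

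*Protocol article*

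**What the plan says.** The label is consistent throughout the protocol article. The opening of Methods/Design gives the primary aim as the effect of using patient portals on clinical outcomes. The text under Fig. 3 says "The clinical effects of the web portal will be investigated using an interrupted times series (ITS) study design". Data analysis says "To investigate the effect of the use of the web portal on the primary clinical outcomes, the ITS data will be analysed". Power calculation credits the whole expected 0.5-point CCQ difference to a portal added to regular disease management. The series is run within groups: "We chose for an interrupted time series (ITS) design to evaluate clinical outcomes (CCQ) within each group".

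The Intervention section then lists several actions.

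- **Group 1:** caregivers are trained in a disease management programme and introduce it in their practices. According to the text under Fig. 3, the programme starts at the same time as the portal. In addition, "all practice nurses will be trained to use the web portal and to communicate with patients according to the principles of self-management".
- **Group 2:** "In group 2 all caregivers (GPs as well as practice nurses) will be trained shortly to ameliorate their skills in COPD care". The statement about practice nurses is repeated for this group. The text under Fig. 3 describes the group's change as "They will start with the web portal, which is integrated in their own disease management program (integrated use") and does not mention the training.
- **Arms 1a and 2a:** the text under Fig. 2 says "In group 1a, high level support implies home visits for patients by a research nurse", and gives 2a telephone consultations by a research nurse.
- **Group 3:** "In group 3 caregivers will not receive any training". There is no active support, and the portal is less advanced than in groups 1 and 2.

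**The concern.** An ITS protects against an underlying trend. It does not protect against a second change introduced at the same point as the one under study, and this plan has no concurrent series without the portal to absorb one. If CCQ stabilises in group 2, better-trained caregivers and the portal are competing explanations. In group 1 a newly introduced programme is a third.

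The primary conclusion is at stake. A reader deciding whether to adopt a portal would be told that the portal produced a benefit that may belong partly to training, to a new care programme or to nurse contact. Data analysis leaves the ITS technique open until the data are complete, but a choice of technique cannot separate components that start together.

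**Working it through.** **Step 1: what each arm receives.** Sources are the text under Fig. 2 and Fig. 3, Intervention, and Power calculation.

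| Arm | Planned n | Portal | Disease management programme | Caregiver training | Research-nurse support |
|---|---|---|---|---|---|
| 1a | 45 | more advanced | new, starts with portal | yes, undated | home visits |
| 1b | 45 | more advanced | new, starts with portal | yes, undated | none |
| 2a | 45 | more advanced | already running | yes, undated | telephone |
| 2b | 45 | more advanced | already running | yes, undated | none |
| 3 | 45 | less advanced | already running | none | none |

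**Step 2: which components certainly fall between the pre and post CCQs.**

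- Group 1's programme does, because it is stated to start simultaneously with the portal.
- The 1a and 2a support does, because it accompanies portal use and so cannot precede it.
- Group 2's training is not dated relative to the first CCQ series. Intervention puts it before the portal offer, and the timing figures are not available. If it was finished before the first CCQs, some or all of its effect lies in the pre-period.
- Group 1's training is undated too, but it prepares the programme that begins with the portal.

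**Step 3: whether another planned analysis separates them.**

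- Arms a and b are randomised within groups 1 and 2, so a minus b within a group estimates the added effect of support. Training, and in group 1 the programme, are common to both arms and cancel out of that contrast. It therefore says nothing about how much of arm b's change belongs to the portal.
- As written, Data analysis compares 1a and 2a with 1b, 2b and 3. Adding group 3 brings a non-randomised cohort into the comparison.
- Groups 1 and 2 against group 3 differ in portal, organisation, training and integration at once. Methods/Design itself says the cohorts cannot be compared by combining data across groups.

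None of these isolates the portal from the training.

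**Step 4: the plan's own sample size.** The inputs are difference 0.5, SD 0.75, two-sided alpha 0.05 (sidedness is assumed, as the article does not state it) and power 80%.

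- Normal approximation: n = 2 × [0.75 × (1.960 + 0.842) / 0.5]² = 35.3, so 36 per group. The two-sample t-test gives 36.3, so 37, which matches the plan.
- Dropout: 37/0.80 = 46.25. The plan prints 45, which equals 36/0.80. The gap is small and not part of this point.
- Total: 2 × 45 = 90 in each of groups 1 and 2, and 90 + 90 + 45 = 225.

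The sizing unit is thus the implementation arm.

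**Step 5: the cost of analysing by arm.** With equal patient-level variance, the standard error of an arm series relative to a care-group series is √(90/45) = 1.41. Group 3 is unaffected, because it is a single arm.

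**The case against.** The strongest reply is that this is an implementation study. Methods/Design says that eHealth is not an isolated intervention, and the nurse contacts check that patients can log on, understand the portal and have begun working on a goal with it. An effect that arises through greater portal use is the mechanism under study, so the contacts can fairly count as delivery. That stands, and the support effect should not be treated wholesale as bias. It does not rescue the label: the quantity is then the portal with its support. It also does not cover training in COPD care, which is not a feature of the portal.

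A reader might infer more than the text supports:

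- **That group 2's training definitely coincides with the interruption.** No date is given, and the order of the Intervention section allows it to have been completed before the first CCQs.
- **That arms a and b will be pooled in the ITS.** The phrase about analysis within each group is ambiguous. The text under Fig. 2 also calls the randomised arms groups, and Power calculation sizes by arm.
- **That one portal effect will be drawn from all patients in groups 1 and 2 combined.** Methods/Design rules out combining data across the three care groups.
- **That the text under Fig. 3 contradicts Intervention by giving group 2 nothing but a portal.** It is silent on the training and does not exclude it.
- **That a definite number of CCQ points is misattributed.** The documents give no effect for training or contacts.
- **That group 3 supplies the missing portal effect.** Its portal is a less advanced one.

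**Conclusion.** The concern holds as a matter of what is being estimated and how it is named. In groups 1 and 2 the ITS estimates the portal plus whatever else starts between the pre and post CCQs. That includes the new programme in group 1 and nurse support in 1a and 2a. It includes caregiver training in group 2 only if that training was not completed before the first CCQ series. Calling these results the effect of the web portal claims more than a within-group series can show.

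The misattribution cannot be expressed in CCQ points from the documents, and the conclusion does not depend on a figure. It rests on the stated contents of the intervention, on the within-group design without a portal-free comparator, and on the absence of any analysis that removes training common to both randomised arms. Group 3, with 45 planned patients, is the only series free of training and active support. Its estimate applies to its own portal.

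**What to change.** In Data analysis, state that the ITS is run by implementation arm, the unit already sized at 45, and label each result by what was delivered:

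- **1b:** portal plus new disease management programme plus caregiver training.
- **2b:** portal plus caregiver training. If training was completed before the first CCQ series, say so and give the dates.
- **1a and 2a:** the corresponding package plus research-nurse support.
- **Group 3:** the only series without training or active support, with a note that its less advanced portal does not stand in for the portal in groups 1 and 2.

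Take the added effect of support from the randomised a/b contrast within group 1 and within group 2, without group 3. Carry the same labels into the aim and the conclusions.

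This changes only analysis and wording. It does not require rescheduling the training, which would be an operational change in a study already under way. The price is a narrower claim about the portal and, compared with a series for a whole care group, 45 rather than 90 patients per series in groups 1 and 2.

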##### Adoption of the portal

Usage of the portal is monitored continuously by log files. User satisfaction is measured by purpose-designed questionnaires.

From the organisational perspective we will measure the following outcome:

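### Log-ins made during support contacts would count as portal adoption only in the high-support arms, tilting the support comparison of use towards the hypothesis by an amount the text does not fix

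*Protocol article*

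**What the plan says.** The Protocol article randomises patients in care groups 1 and 2 to high (a) or low (b) support. The text after Fig. 2 describes the high level for the first care group: "In group 1a, high level support implies home visits for patients by a research nurse who accompanies the use of the web portal". The second care group has a remote version of the same thing: "In group 2a, high level support implies telephone consultation for patients by a research nurse who accompanies use of the web portal". The Intervention section confirms who is included ("a subgroup of participants (1a and 2a) will receive extra support to use the portal by home visits or with instructions by telephone") and then sets out what happens at these contacts: "During the home visit and consultation it will be checked if patients are able to log on the portal". The same contacts check comprehension of what the portal offers and whether work on the health goal has begun.

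In 1b and 2b the primary care nurse demonstrates the portal once, "without any follow-up instruction". For group 3: "There will be no active support from caregivers or research nurses". Both randomised arms share the start: "All patients in group 1 and 2 start with a personal instruction by the primary care nurse during a regular control visit".

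The outcome is set under Adoption of the portal: "Usage of the portal is monitored continuously by log files". No rule there or under Data analysis sets apart sessions held with the research nurse. Data analysis compares 1a plus 2a with 1b, 2b and group 3 together, by chi-square or Fisher tests for categorical variables and F-tests or ANOVA for continuous ones.

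**The concern.** The randomised intervention consists partly of using the portal in a nurse's company, and the outcome is portal use. If the patient logs in during the contact, the log file records delivery of the intervention as a response to it. Randomisation gives no protection, because the extra log-ins arise after allocation and in one arm only.

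The direction is that of the hypothesis in Methods/Design and the Discussion, that more personal support brings more use. High against low support within groups 1 and 2 is also the study's only randomised contrast. A positive result on raw log-ins could not be told apart from the nurses having carried out their visits.

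**Working it through.** **Which sources of log-ins differ by arm**

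- Nurse intake: common to a and b, so it cancels within groups 1 and 2. Group 3 has none.
- Portal questionnaires (Data collection): offered in every arm, so not differential by design.
- Support contacts: 1a and 2a only. Nothing in the other arms offsets them.

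**Inputs from the plan.** The article gives no figure for adoption. Its only sample size is for the CCQ: difference 0.5, SD 0.75, 80% power, alpha 0.05, giving 37. A two-sided two-sample t calculation gives 36.3, rounded up to 37, so the figure reproduces if read as per arm. The plan then takes 45 per arm, which gives 1a + 2a = 2 × 45 = 90 and 1b + 2b + 3 = 3 × 45 = 135.

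**Assumptions, not in the text**

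- Each high-support patient logs in k = 1, 2 or 3 times during contacts.
- Unprompted log-ins are negative binomial with mean m = 2, 5 or 15 and dispersion 1 in every arm.
- Support has no effect on unprompted use.

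**Bias.** Expected difference = (m + k) − m = k.

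**Size relative to noise.** The variance is m + m². For 90 against 135, SE = √[(m + m²)(1/90 + 1/135)]:

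- m = 2: √(6 × 0.01852) = 0.33, so k = 1 is 3.0 standard errors.
- m = 5: √(30 × 0.01852) = 0.75, so k = 1 is 1.3 standard errors.
- m = 15: √(240 × 0.01852) = 2.11, so k = 1 is 0.47 standard errors.

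**Simulated rejection rate, Welch t-test, two-sided 5%, no true effect (4,000 runs per cell)**

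| Comparison | m | k = 0 | k = 1 | k = 2 | k = 3 |
|---|---|---|---|---|---|
| 1a+2a v 1b+2b+3 (90 v 135) | 2 | 0.05 | 0.86 | 1.00 | 1.00 |
| | 5 | 0.04 | 0.25 | 0.76 | 0.98 |
| | 15 | 0.05 | 0.07 | 0.16 | 0.30 |
| 1a+2a v 1b+2b (90 v 90) | 2 | 0.05 | 0.79 | 1.00 | 1.00 |
| | 5 | 0.05 | 0.24 | 0.68 | 0.95 |
| | 15 | 0.05 | 0.07 | 0.14 | 0.26 |
| a v b in one care group (45 v 45) | 2 | 0.05 | 0.51 | 0.96 | 1.00 |
| | 5 | 0.05 | 0.14 | 0.41 | 0.72 |
| | 15 | 0.05 | 0.06 | 0.10 | 0.16 |

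The k = 0 column is what remains when support-session log-ins are excluded: the error rate is nominal.

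**Cross-check with another spread.** Take the randomised contrast after 20% drop-out, 90 × 0.80 = 72 per arm, and log-in SD 4, 6 or 10 (assumed). SE = SD × √(2/72) = SD/6. Normal-approximation rejection rates are 0.32, 0.17 and 0.09 for k = 1, and 0.85, 0.52 and 0.22 for k = 2. The range is again wide and the direction the same.

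**The case against.** **The article names a data source, not a metric.** The full protocol or analysis plan may define use in a late window, where the artefact would be small or absent. That is fair, and asking only for a missing definition would be no finding. What stands is that two stated features collide: accompanied use in one arm, and continuous logging as the measure of adoption. Log files used as stated give a biased contrast.

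**A log-in at every contact is an inference.** A reader might conclude that high support wins by construction, with each visit or call written to the log as patient use. The text does not say so. Accompanied use at a home visit makes a log-in likely, but a telephone check may be verbal.

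**The sizes are assumed.** This stands. Data collection and the ITS description also imply up to 4 × 3 = 12 questionnaire occasions per patient in the portal, so raw means of 2 or 5 may be too low. That helps only in part, because the spread of counts governs the false-positive rate. Log-ins that every patient makes raise the mean without adding spread.

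**Ever having logged in.** A reader might also infer that this proportion must approach 100% under high support and differ significantly. Since all arms have questionnaires in the portal, and groups 1 and 2 an intake, a binary measure is weak evidence here, and the point does not rest on it.

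**Accompanied use may be part of what the support package achieves.** That is a legitimate quantity in an implementation study, and a reason to report the unfiltered count too. It does not answer whether support makes patients use the portal more on their own.

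**Conclusion.** The point holds in a limited form. Any log-in made during a support contact counts in 1a and 2a with no counterpart in 1b, 2b or group 3, and so pushes the support comparison of use towards the hypothesis. The direction follows from the text, provided that at least some contacts involve a log-in. The size does not. Under the assumptions above, false-positive rates for a nominal 5% test run from about 0.06 (one contact, heavy use, one care group) to about 1.00 (two or three contacts, light use).

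The comparison of groups 1 and 2 with group 3 is affected in the same direction only if patients log in during the nurse intake, which the text does not state. The artefact does not enter the CCQ, which is the primary outcome. Adoption is a secondary outcome, but it carries a stated hypothesis, so the plan should be changed.

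**What to change.** For the support comparison, define log-file use as patient-initiated use. Exclude every session on the date of a home visit, support call or practice-nurse intake, by one rule in all arms. Report the unfiltered count as a sensitivity analysis. Sessions on later days stay in, since they are the effect of interest.

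This needs contact dates. The Costs section says that the research group administers implementation costs, mainly for home visits and telephone interviews, but mentions no dates. The group should therefore record the date of each contact alongside the cost.

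The cost is a sentence in the outcome definition, a date field, and matching of log dates to contact dates. A few genuine self-initiated sessions on contact days are lost. With three contact days in 15 months of portal access (about 15 × 30 = 450 days), that removes 3/450 = 0.7% of the observation time in a high-support patient. Design, visits and sample size are unchanged.
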